### Recruitment {36}

Support for enrolment will be provided by dental professionals, as appropriate, in the form of an interpreter and multimedia participant information resources hosted on a patient-facing trial website. Our patient and public involvement and engagement (PPIE) work has suggested several ways to improve involvement of children and parent/carers including using a multimedia participant information resource, offering branded stationery appealing to children and ‘thank you’ shopping vouchers.

It should also be noted that the main trial will only progress following satisfactory outcomes from an initial internal pilot trial. This will be based on the number of dental sites open to participant recruitment, the child (and parent/carer) recruitment rate in total and by site and month, and the number and percentage of participants randomised to receive the intervention who are engaging in the intervention (based on completion of the ‘message to dentist’ component of the self-help CBT resources).

In addition to monitoring overall participant recruitment rates, we will also monitor recruitment of participants living in deprived areas, based on the Index of Multiple Deprivation quintiles derived from participants’ postcodes, to ensure those living in the most deprived areas of England and Wales are included. This will be reported along with the progression criteria and changes will be made to the recruitment strategy to improve recruitment of those living in the most deprived areas if required.

At the end of the internal pilot, the response rate for the parent/carer questionnaire, which includes the resource use questionnaire, will be determined, and the choice of approach to data collection reviewed.

### Assignment of interventions: allocation

#### Sequence generation {16a}

The randomisation sequences will be generated by a statistician in York Trials Unit, UK (YTU). Randomisation of children will be 1:1 and stratified by site using variable block sizes. The statistician will also randomly select which dental health professionals will deliver the CBT intervention or usual care.

#### Concealment mechanism {16b}

The randomisation sequence will be concealed using a secure, remote web-based randomisation service at YTU.

#### Implementation {16c}

Following the child’s initial assessment by a dental professional, site staff will enter key participant details into a dedicated Trial Management System (TMS) to confirm eligibility and then randomise the participant. The TMS will inform the site staff of the allocation, which will be communicated to the participant and an appointment made with the relevant dental professional for the subsequent treatment visits. Participating dental professionals will be informed of whether they will be delivering the intervention or usual care by a trial manager with details of appropriate training provided.

### Assignment of interventions: blinding

#### Who will be blinded {17a}

Due to the open nature of the intervention, it will not be possible to blind participants, their parents/carers or treating DPs to group allocation. Members of the research team, the statistician and health economist will not be blinded.

#### Procedure for unblinding if needed {17b}

This is an open trial so there is no procedure for unblinding.

## Data collection and management

### Plans for assessment and collection of outcomes {18a}

#### Dental data

Data from dental sites and participating DPs will be collected at baseline, and throughout the 12-month follow-up period via paper-based CRFs (see appendices). Information will be sought on: need for referral to secondary care; use of sedation or GA to complete the course of planned treatment; attendance patterns of the patients; Clinical Global Impressions Improvement score (1–7) as an indicator of the DP’s perception of the degree of improvement in the child’s DA at the end of treatment. Additionally, following recruitment, DPs will also provide baseline data on (1) the socio-demographic characteristics of participants, including age, gender, ethnicity and postcode; (2) their clinical status including: caries experience (number of decayed, missing and filled teeth (dmft/DMFT)), and previous experience of local anaesthetic, sedation or GA, and (3) information as to whether the dental professionals involved in the trial from that site had ever previously seen the patient.

#### Child participants

As described previously, children will complete three validated measures to record self-reported anxiety (MCDAS); OHRQoL (CARIES-QC) and HRQoL (CHU9D) at baseline, FU1 and FU2 [27–29].

#### Parent/carer participants

Self-administered paper questionnaires will be used to collect personal data (age, gender, ethnicity, postcode of the participating child) and outcome measures from the parent/carer of participating children at baseline, FU1 and FU2. Additionally, parents/carers will report on their own degree of DA using the validated MDAS [30]. Further costs (e.g. travel time/costs for attending appointments, time missed from school, time off work for parent/carer/carers, out of pocket expenditure on medications) will also be collected via parent/carer questionnaires (for the secondary analysis, societal perspective).

### Plans to promote participant retention and complete follow-up {18b}

Child and parent/carer participants will be offered branded stationery at follow-up timepoints and given a shopping voucher (value 10 GBP) at the final follow-up appointment to thank them for taking part.

### Data management {19}

Sheffield Teaching Hospital (STH) and YTU will hold joint data controller responsibilities and will comply with all aspects of the General Data Protection Regulation 2016 applicable in the UK from May 2018.

A bespoke trial management system (TMS) will be created for the trial which will house information on questionnaire due and return dates, as well as site and participant-level data. A unique trial identification number (Trial ID) will be generated for each participant and their parent/carer at the time of entering their details into the TMS.

Paper-based forms collecting outcome data (identified only by Trial ID and returned to YTU) will be logged and then scanned using optical scanning techniques (Cardiff Teleform). Scanned data will be 100% validated and cross-checked with the information in the management database. Once received by YTU, paper consent forms and paper data (identified by Trial ID only) will be held separately and securely in a controlled access area in locked cabinets, at the University of York. Sites will keep a paper copy of consent forms for their records. This is the only participant documentation that will be retained at the sites.

YTU will be responsible for secure data archiving, and secure data deletion.

### Confidentiality {27}

Confidentiality of participants will be protected firstly through the allocation of a unique trial ID number. There will be restricted access to any personal data as both the TMS and the data management systems are held on secure University of York servers, with access limited to specified members of YTU staff as detailed in a delegation log. Personal data will be processed under Article 6 (1) (e) (processing necessary for the performance of a task carried out in the public interest) and Special Category data under Article 9 (2) (j) (processing necessary for scientific research purposes) of the General Data Protection Regulation 2016. After the trial personal information will be stored securely until the planned deletion date.

### Plans for collection, laboratory evaluation and storage of biological specimens for genetic or molecular analysis in this trial/future use {33}

This study does not involve the collection or storage of any human material.

## Statistical methods

### Statistical methods for primary and secondary outcomes {20a}

Analyses will be conducted in accordance with YTU standard operating procedures and will be undertaken in Stata v16 or later (to be confirmed in the final report). Statistical tests will be two-sided at the 5% significance level. All analyses will be conducted on an intention-to-treat basis, including all children in the groups to which they were randomised, irrespective of deviations based on non-compliance (unless otherwise specified).

The MCDAS scores at FU1 and FU2 will be compared between groups using a covariance pattern linear mixed model, adjusting for baseline scores, other pertinent baseline covariates, time and an interaction between treatment group and time as fixed effects. Child, treating dental professional and region will be included as random effects. The adjusted mean difference in MCDAS score at each time point will be extracted with its 95% confidence interval and *p*-value; the treatment effect at FU2 will be the primary endpoint, while the difference at the end of the course of treatment (FU1) is a secondary endpoint.

As part of the CALM trial, an anchor-based approach will be used to determine the change in MCDAS that represents the minimum clinically important difference (MCID). The use of multiple, independent anchors is recommended to produce a range of MCID scores for the MCDAS based on the different anchors. The ‘anchors’ will include the GRC item, the CGI-I item and clinical outcomes, including referral to specialist services and the use of sedation or GA.

CARIES-QC and parent/carer DA will be analysed in an analogous way to that described for the MCDAS.

The need for referral to secondary care and use of sedation or GA will be analysed by mixed effect logistic regression, adjusting for baseline MCDAS score and other pertinent baseline covariates as fixed effects, and dental team member and dental site as random effects. Treatment provided (e.g. prevention, restoration, extraction), attendance patterns (attended or missed appointments) and duration of attended appointments will be summarised for the two groups.

Baseline characteristics or changes in process variables that could affect the primary outcome between participants who received the intervention and participants who received usual care will be examined. Baseline and follow-up questionnaires will be analysed using linear regression modelling to measure mechanisms of impact. Data from CRFs will be compared within and between intervention and usual care to measure aspects of implementation.

The economic evaluation will assess the cost-effectiveness of the intervention versus usual care, by means of (1) a within-trial economic analysis over the trial’s 12-month time horizon, and (2) a decision analytic model, to extrapolate beyond the trial. An NHS and personal social services perspective will be taken in the base case, with a secondary analysis exploring a broader perspective. NICE recommendations will be followed wherever possible [36]. The primary economic analysis will take the form of a cost-utility analysis, to estimate the mean differences in costs and QALYs, using the CHU9D to generate utilities. In addition, a cost-effectiveness analysis will incorporate the MCDAS score (i.e. the trial’s primary outcome) as the effectiveness measure. Analyses will be undertaken on an intention-to-treat basis, in Stata v17 or later, utilising data recorded by dental practices and via self-completed questionnaires (by participants and parents/carers) regarding participants’ outcomes, resource use and costs.

Specifically, questionnaires will be completed at baseline, at the end of the course of treatment and at 12 months. Unit costs, sourced from established databases [37, 38], will be applied to each resource item to estimate a total cost per participant. Cost estimates of the intervention will incorporate the time spent delivering the intervention and undertaking the associated training, with the costs of sedation/GA referrals also included. Further costs incurred by parents/carers of participants will be collected for the secondary analysis (e.g. time off work, travel costs for appointments). Time missed from school in relation to appointments/DA will be listed as a ‘consequence’ and compared between groups, but not formally valued in monetary terms.

QALYs will be estimated for each participant using the area under the curve approach [39]. Costs will be presented in UK GBP for the appropriate year. Mean within-trial estimates of costs and health benefits will be calculated using regression methods, and multiple imputation methods will be used to deal with missing data [40], with sensitivity analysis exploring a complete case analysis. The results will be presented in terms of incremental cost-effectiveness ratios and net health benefit at 12 months. Uncertainty will be described using confidence intervals and cost-effectiveness acceptability curves [41], and sensitivity analyses will explore the impact of underlying assumptions and key parameters of the analysis in terms of the cost-effectiveness results. A pre-specified health economics analysis plan will be agreed with the trial’s independent groups.

Depending on the trial’s findings, the economic results will be modelled beyond the time horizon of the trial, making assumptions of a longer-term impact. Prior to undertaking the within-trial economic analysis, a modelling plan will be developed. The model will use data collected from the trial (outcomes, resource use, attendance patterns, referrals), supplemented by published data. Future costs and health benefits will be discounted in line with NICE recommendations [36]. Sensitivity analyses will explore uncertainty around model parameters, with the robustness of results tested using different scenarios.

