**Methods:**

This 4-year randomised controlled trial will involve 600 children (aged 9–16 years) and their parent/carers in 30 UK primary dental care sites. At least two dental professionals will participate in each site. They will be assigned, using random allocation, to receive the CBT training and deliver the intervention or to deliver usual care. Children with DA attending these sites, in need of treatment, will be randomly allocated to be treated either by the intervention (CBT) or control (usual care) dental professional. Children will complete questionnaires relating to DA, OHRQoL and HRQoL before treatment, immediately after treatment completion and 12 months post-randomisation. Attendance, need for sedation/GA and costs of the two different approaches will be compared. The primary outcome, DA, will be measured using the Modified Child Dental Anxiety Scale. Scores will be compared between groups using a linear mixed model.

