### Sample size {14}

From the feasibility study [21], the MCID for the MCDAS was calculated as 5 points using the anchor-based method, and the standard deviation was 6.5. Given the small sample size of the feasibility study, this trial will be powered to detect a more conservative difference of 2.5. The clustering of patients within dental professionals’ lists within sites, using an average cluster size of 20 (patients per dental site), and an intra-cluster correlation coefficient (ICC) of 0.03 is used in the sample size calculation. To detect a 2.5 point difference, assuming 90% power, 5% alpha, SD of 6.5, average cluster size of 20, ICC of 0.03 and 20% attrition, the study would need to recruit 600 children (involving 30 dental sites and 60 dental professionals). Based on the literature, it is estimated that 80% of parents/carers who are approached for the study will agree to take part; hence, it is envisaged that 750 children will need to be approached to take part [34, 35].

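### The primary mixed model leaves out dental site, the stratification factor that holds both arms' professionals; to the extent that sites differ, its standard error is too large (0 to about 12% at the planned ICC)

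*Protocol article*

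**What the plan says.** All places are in the protocol article.

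- **Primary model** (Statistical methods {20a}): MCDAS at the two follow-ups is analysed with a covariance pattern linear mixed model. Of its random effects the section says: "Child, treating dental professional and region will be included as random effects". Site is named neither there nor among the fixed effects. CARIES-QC and parent/carer dental anxiety are to be analysed in the same manner.
- **Binary outcomes** (same section): the models for referral and for sedation or GA have "dental team member and dental site as random effects".
- **Randomisation** (Sequence generation {16a}): "Randomisation of children will be 1:1 and stratified by site using variable block sizes".
- **Site structure** (Abstract, Methods): "At least two dental professionals will participate in each site", and children "will be randomly allocated to be treated either by the intervention (CBT) or control (usual care) dental professional".
- **Sample size {14}**: patients are described as clustered in professionals' lists within sites. A single ICC of 0.03 is applied to an average of 20 patients per site, giving 600 children, 30 sites and 60 professionals. The ICC is not divided between site and professional.

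**The concern.** The design compares the two arms inside each site. Anything that raises or lowers anxiety scores for a whole site (case mix, deprivation, premises, local habits) affects both arms equally and cancels from the treatment contrast. An analysis benefits from that cancellation only if it knows which professionals belong to the same site.

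The primary model does not. With about one professional per arm per site, the professional random effect absorbs the site variance, and the model treats the 60 professionals as unrelated apart from region. Region has only five levels and removes only differences between regions. Variance that has cancelled from the estimate therefore stays in its standard error.

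At stake are the width of the confidence interval and the calibration of the p-value for the primary outcome and the two outcomes that copy its model. The primary model also departs, without a stated reason, from the randomisation, from the nesting described in the sample size section and from the neighbouring logistic models.

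**Working it through.** **1. The plan's own figure.** The inputs from Sample size {14} are "To detect a 2.5 point difference, assuming 90% power, 5% alpha, SD of 6.5", cluster size 20, ICC 0.03 and 20% attrition. Tests are two-sided at 5% ({20a}).

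- Per arm without clustering: 2 × (1.960 + 1.282)² × 6.5² / 2.5² gives 143.
- Design effect: 1 + 19 × 0.03 = 1.57, so 225 per arm and 450 in total.
- With attrition: 450 / 0.8 = 563. Thirty sites of 20 give 600.
- At 600 recruited and 480 analysed, the planning SE is √(2 × 42.25 × 1.57 / 240) = 0.743 and power is 92.0%. The stated 90% is met.

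**2. Layout for the check.** 60 professionals / 30 sites = 2 per site; 480 / 60 = 8 analysed children per professional. Equal sizes, one follow-up time and no baseline adjustment are simplifying assumptions. Total variance is 6.5² = 42.25, split into site (V_S), professional (V_P) and residual (V_E). With ICC 0.03, V_S + V_P = 1.2675 and V_E = 40.9825, so V_E / 8 = 5.123.

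**3. Formulas.**

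- Actual variance of the treatment difference, and the variance reported with site in the model: (2/30)(V_P + V_E/8).
- Variance reported without site: (2/30)(V_S + V_P + V_E/8).
- Actual two-sided type I error without site: 2[1 − Φ(1.96 × ratio of the two SEs)].

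For example, with all clustering at site level: √(0.0667 × 6.390) = 0.653 reported, against √(0.0667 × 5.123) = 0.584 actual.

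**4. Results at ICC 0.03.** The article does not give the split, so the whole range is shown.

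| Clustering lies | SE without site | SE with site | Inflation | Type I error without site |
|---|---|---|---|---|
| all by professional | 0.653 | 0.653 | 0% | 5.0% |
| half and half | 0.653 | 0.619 | 5% | 3.9% |
| all by site | 0.653 | 0.584 | 12% | 2.9% |

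**5. Simulation with region in the model** (5 regions of 6 sites, 40,000 replicates, professional-level means).

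| Clustering lies | Null rejection, without / with site | Power for 2.5 points, without / with site |
|---|---|---|
| all by professional | 4.9% / 4.9% | 96.4% / 95.9% |
| half and half | 4.0% / 4.9% | 97.2% / 97.4% |
| all by site | 3.2% / 5.1% | 97.8% / 98.5% |

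In the last row the mean reported SE without site was 0.645, against an empirical spread of the estimate of 0.585 to 0.590. That is about 10% too large. No case gave an SE that was materially too small.

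**6. Sensitivity.** If the ICC were 0.01, 0.05 or 0.10 (assumptions), the largest inflation, with all clustering by site, would be 4%, 19% or 37%. The 12% figure is for equal site sizes. One calculation with unequal sizes (also an assumption, as only the average is given) at ICC 0.03 gave 0.673 reported against 0.588 actual, a ratio of 1.14 in the same direction.

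**The case against.** **The size is unknown and may be nil.** This stands. The inflation exists only if sites differ beyond region, baseline MCDAS and other covariates. A single undivided ICC does not show that they do, and baseline adjustment may shrink the difference. A reader might infer that the reported SE is certainly too large and the type I error well below 5%. The article supports only the conditional statement; with an equal split the type I error is about 4%.

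**Planned power is not at risk.** This also stands. The SE of 0.653 from the model as written is still below the planning SE of 0.743. Power for 2.5 points is about 96 to 98% in the simulation. A serious loss appears only with larger ICCs or smaller effects than the article states.

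**Site might enter through the other baseline covariates, or be left to the SAP.** This is weak. The logistic models use the same general reference to covariates and still name site separately. The primary model's random effects are listed outright, so this is a stated choice and not an omitted detail.

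**The plan does not contradict itself.** This is fair. Different outcomes have different models, so it is an unexplained inconsistency and not two incompatible statements about one analysis.

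**Other readings of the same sentence.** A reader might infer that the child random effect is redundant. That depends on an unstructured residual pattern, which the article does not specify. A reader might also infer that the treating professional is a post-randomisation variable. Under the stated intention-to-treat rule, with children allocated to a professional's care, the term can reasonably mean the assigned one. Whether region is random or fixed is a matter of preference. None of these is part of this point.

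**Conclusion.** The point holds in a limited form and is one that should be fixed. The omission and its direction are certain from the text and the design. The size is not: at the planned ICC of 0.03 and equal sizes, the SE inflation is between 0 and about 12% and the actual type I error between about 3 and 5%, depending on a site/professional split that the article does not give. The error is conservative. It does not bias the treatment estimate, does not raise the false-positive rate, and leaves power for 2.5 points above the stated 90%. The loss is attainable precision and agreement between the analysis and the way children are randomised. The figures assume two professionals per site and 8 analysed children each; they ignore baseline adjustment, which could reduce the inflation.

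**What to change.** In Statistical methods {20a}, and in the SAP if it repeats the sentence, add dental site to the primary MCDAS model as a random or fixed effect, with dental professional nested within site as a random effect. Apply the same change to the CARIES-QC and parent/carer dental anxiety models. This brings them into line with the referral and sedation/GA models. Child and region can stay as they are.

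The cost is one sentence and no new data. If all clustering turned out to be by professional, the extra term would cost about half a percentage point of power (96.4% to 95.9% in the simulation). Because the trial statistician is not blinded (Who will be blinded {17a}), the change should be recorded before outcome data are analysed by arm, so that it is not a later unplanned alteration of the primary model.
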